
## Data Availability

Data availability is not applicable to this article as no new data were created or analysed in this report.

## Appendix 1

### Eligibility criteria

Inclusion criteria

- Adult out-patients age 18 years and above
- Diagnosis of DSM-5 bipolar disorder (both bipolar disorder I and bipolar disorder II), currently in remission, confirmed by Structured Clinical Interview for DSM-5 (SCID)
- Currently euthymic (17-item Hamilton Rating Scale for Depression score <8 and Young Mania Rating Scale score <8)
- Able to give informed consent
- On stable psychiatric medication regimen for at least 3 months
- Resident of the trial catchment area.

Exclusion criteria

- Active substance use disorder, based on DSM-5 criteria
- Currently experiencing recurrence (mania, hypomania, mixed or depressive
- Active suicidal ideation
- Unstable residential arrangements that reduce likelihood of being available for the duration of trial.

## Appendix 2

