### Outcome measures

The primary outcome measure is time (in weeks) to recurrence of a mood (depressive/manic/hypomanic/mixed) episode. This will be assessed at each follow-up using the Longitudinal Interval Follow-up Evaluation (LIFE),^29^ an integrated system for assessing the longitudinal course of psychiatric disorders. The assessment will consist of a semi-structured interview, during which an interviewer uses the LIFE to collect detailed psychosocial, psychopathological and treatment information for the follow-up interval. The weekly psychopathology measures are ordinal symptom-based scales with categories defined to match the criteria of DSM-5. Additional secondary measures are listed in Appendix 3.

All scales (both self-report and clinician-rated) will be administered using a tablet, to allow results to be safely and instantly loaded to the study database, with paper versions available if there are technological difficulties. All scales will be translated into Urdu and back-translated into the original language. Most have been used in previous studies in Pakistan, including our pilot.^24^

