### Statistical analysis

The intention-to-treat principle will be used, with participants analysed according to their allocated group. Our primary outcome is time to recurrence observed within 12 months. The treatment effect will be evaluated using the Cox proportional-hazards model with treatment assignment as the primary predictor. Baseline measures of key clinical characteristics (duration of illness, number of previous episodes) and demographics (age, gender, self-reported biological sex) will be controlled in the model. The treatment effect will be illustrated by the estimated hazard ratio to relapse between the two groups. In addition, parametric survival analysis models^38^ will be employed when appropriate. In the widely used Weibull distribution case (for example), the parametric analysis will use a log-linear model on the scale parameter with treatment assignment as the primary predictor while controlling for the set of covariates described above. The regression coefficient on treatment assignment can be interpreted as the log hazard ratio between the two treatment conditions in terms of relapse. This will help estimate the mean time to recurrence for the two groups. As this is a multicentre trial, dependencies for participants from the same centre will be accounted for by including centre as a random effect.^25^ We will investigate levels of missing data, assumptions (e.g. missing at random) and predictors of missingness. Missingness will be addressed using multiple imputations, capitalising on fitting mixed models with maximum likelihood and appropriate sensitivity analyses.^39^ We will also conduct an exploratory mediation analysis to investigate the role of treatment adherence and bipolar disorder type (I or II) on 12-month outcomes. Statistical inference will be conducted using two-tailed tests with 0.05 as the level of significance and 95% confidence intervals with secondary outcomes adjusted for multiple comparisons as necessary. We will use the most appropriate analytic and graphical features of SPSS, STATA and R as relevant.

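### No minimum time in remission is set and time well at entry is not in the primary Cox model, so an early return of the index episode can count as the primary recurrence event

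*Protocol article*

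**What the plan says.** Appendix 1 (Eligibility criteria) has three mood criteria:

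- a diagnostic criterion, bipolar I or II disorder "currently in remission, confirmed by Structured Clinical Interview for DSM-5 (SCID";
- a separate cut-off on two symptom scales, "Currently euthymic (17-item Hamilton Rating Scale for Depression score <8 and Young Mania Rating Scale score <8";
- exclusion of anyone "Currently experiencing recurrence (mania, hypomania, mixed or depressive".

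The only eligibility criterion with a look-back period is "On stable psychiatric medication regimen for at least 3 months".

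The Outcome measures section states: "The primary outcome measure is time (in weeks) to recurrence of a mood (depressive/manic/hypomanic/mixed) episode". It is rated with the LIFE at each follow-up. The Statistical analysis section sets the horizon ("Our primary outcome is time to recurrence observed within 12 months") and then uses another word for the same event: "The treatment effect will be illustrated by the estimated hazard ratio to relapse between the two groups". The Sample size section likewise gives time to recurrence for TAU and relapse time for CaPE.

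The covariates of the primary Cox model are "Baseline measures of key clinical characteristics (duration of illness, number of previous episodes" together with age, gender and sex; centre is a random effect. The randomisation strata are site, bipolar type and sex. Appendix 3 schedules the SCID/LIFE at baseline and at months 3, 6 and 12.

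**The concern.** The first study objective concerns recurrence in people who are in remission. A patient whose episode ended very recently and a patient who has been well for years both meet the mood criteria as written. If the first patient's symptoms return within weeks, that may be the old episode resurfacing rather than a new one, and the article states no rule that separates the two.

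Two things are at stake. The first is meaning: a hazard ratio that mixes relapse of the index episode with recurrence of a new one is harder to read against the stated objective. The second is precision: time well at entry is a plausible prognostic factor for time to the next episode, yet it is not a stratum, a model covariate or a subgroup variable. In a Cox model, leaving out a prognostic factor tends to pull the estimated hazard ratio towards 1, even under randomisation.

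**Working it through.** **1. Reading the criteria side by side.** The SCID remission criterion, the score cut-offs and the exclusion all describe the present state, and none states a duration. The stable-medication rule makes entry straight after an acute, actively treated episode less likely. It does not exclude it, since an episode can end on an unchanged regimen. So recent remission is compatible with entry, but how common it would be is not stated.

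**2. Reproducing the plan's power.** Inputs from Sample size: TAU mean 21.4 weeks, CaPE mean 34.2 weeks, 120 per arm, hazard ratio (HR) 1.60, stated power 0.91. The two-sided 0.05 level is from Statistical analysis. Exponential times are assumed.

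- Events over T weeks = 120 × (1 − exp(−T/21.4)) + 120 × (1 − exp(−T/34.2)).
- T = 52: 109.4 + 93.8 = 203. T = 48: 107.3 + 90.5 = 198.
- Power = Φ(√events/2 × ln 1.60 − 1.96) = 0.918 at T = 52 and 0.911 at T = 48.

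This agrees with 0.91, and 240/0.80 = 300 matches the recruitment target. The point exposes no arithmetic error.

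**3. How many events fall early, of any kind.** By week 8 the TAU probability is 1 − exp(−8/21.4) = 0.31 and the CaPE probability is 1 − exp(−8/34.2) = 0.21. Over 52 weeks the TAU probability is 1 − exp(−52/21.4) = 0.91, so 0.312/0.912 = 34% of 12-month TAU events occur by week 8. This shows that early events carry weight. It does not show what share of them would be return of the index episode.

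**4. Illustration only.** Suppose a share of participants has recently remitted and CaPE has no effect on them in weeks 0–8, with HR 1.60 otherwise. The share, the zero early effect and the doubled hazard are all assumptions. Simulated Cox fits (n = 240, 52 weeks) give approximately:

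| Recently remitted (assumed) | Their early hazard | Estimated HR | Power |
|---|---|---|---|
| 0% | – | 1.60 | 0.92 |
| 20% | unchanged | 1.55 | 0.87 |
| 40% | unchanged | 1.50 | 0.81 |
| 20% | doubled | 1.52 | 0.84 |
| 40% | doubled | 1.44 | 0.74 |

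For reference, the plan's minimum detectable HR at 0.80 power is 1.49.

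**5. The price of a minimum remission period.** If such a rule lengthened the TAU mean time (assumed values), with HR 1.60, 240 participants and 52 weeks, the formulas in step 2 give:

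| TAU mean (weeks) | Events | Power |
|---|---|---|
| 30 | 178 | 0.88 |
| 40 | 154 | 0.83 |
| 52 | 132 | 0.77 |

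These losses overlap those in step 4, so a net gain in power from restricting entry is not shown.

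**The case against.** Several stronger readings are tempting, and the documents do not support them.

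- **That index-episode relapse is being counted as recurrence.** Only that it can be. The article has no data on time since the last episode, and the rule for declaring an event from the weekly LIFE ratings may sit in the full protocol, which is not shown. SCID-confirmed remission is a separate criterion from the score cut-offs, and what it implies about duration depends on definitions outside this document.
- **That the treatment comparison is biased.** It is not. Randomisation spreads recently remitted participants over both arms.
- **That early events dilute the effect because of who is admitted.** Relapse detection and response are sessions 7 and 8 of 12 weekly sessions for every CaPE participant, including those long well. If CaPE had no effect on anyone before week 8, the same simulation gives HR about 1.35 and power about 0.56. That would come from the delivery schedule, and an entry rule would not cure it.
- **That a minimum remission period is required.** Broad entry is a legitimate choice for an effectiveness trial that aims for a representative sample, and a restriction costs events.

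These objections stand. They limit the claim but do not remove it: the eligibility list states no remission duration, the article uses two terms for one event, and the stated covariates omit time well at entry.

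**Conclusion.** The point holds as one of interpretation and precision, not of bias or faulty arithmetic. The criteria as printed admit participants who have only just remitted. An early return of their episode can count as the primary event, and the primary model does not account for how long each participant has been well.

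The size of any effect on the hazard ratio or power cannot be derived from the documents. The ranges in the working depend on an assumed 20–40% share, an assumed absence of early effect and, in two rows, an assumed doubling of hazard. They show what is possible, not what is expected. That time well at entry is prognostic is plausible, but it is a judgement and not a figure from the article. Adjusting for it is worthwhile because the cost is so low.

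**What to change.** 1. **Covariate.** Derive weeks since the end of the last mood episode from the baseline SCID/LIFE and add it, with its functional form stated, to the prespecified covariates of the primary Cox model. Do this before any unmasked analysis. Cost: at most one degree of freedom if it enters as a single linear or transformed term, against about 200 expected events, with no new visit or instrument. The sponsor should confirm that the baseline interview records the date the last episode ended, including for participants who have been well for a long time. Adjustment addresses prognosis; it does not classify an individual event as relapse or recurrence.
2. **Terminology.** Use one term for the primary event throughout Outcome measures, Sample size and Statistical analysis. If relapse of the index episode is meant to count, say so. Cost: wording only.
3. **For the sponsor to weigh.** A minimum remission period in Appendix 1 would sharpen the meaning of recurrence but would narrow the sample and lower the event rate (step 5 of the working). No duration is proposed. If entry stays broad, summarising time since the last episode by arm would let readers judge how far early relapse contributes.

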### Sessions of the culturally adapted psychoeducation (CaPE) intervention

Session 1: Concept and causes

Session 2: Symptoms (mania, hypomania, depression and mixed conditions)

Session 3: Evolution and prognosis, psychoactive substance misuse

Session 4: Treatment with medication (mood stabilisers, antipsychotics, antidepressants)

Session 5: Alternatives therapies

Session 6: Risks associated with interruption of treatment

Session 7: Learning to detect early symptoms of relapse

Session 8: What to do when a relapse is detected

Session 9: Regularity of habits

Session 10: Stress control

Session 11: Problem-solving strategy

Session 12: Final session

## Appendix 3

### Assessment schedule

**Table d64e765:**

Instrument	Baseline	Month 3	Month 6	Month 12
Demographic questionnaire	✓			
SCID Longitudinal Interval Follow-up Evaluation (LIFE)^29^	✓	✓	✓	✓
Young Mania Rating Scale (YMRS)^30^	✓	✓	✓	✓
17-item Hamilton Rating Scale for Depression (HRSD-17)^31^	✓	✓	✓	✓
EuroQol-5D (EQ- 5D)^32^	✓	✓	✓	✓
Bipolar Recovery Questionnaire (BRQ)^33^	✓	✓	✓	✓
4-item Morisky Medication Adherence Scale (MMAS-4)^34^	✓	✓	✓	✓
Bipolar Knowledge and Attitudes Questionnaire (BKAQ)^33^	✓	✓	✓	✓
Client Service Receipt Inventory (CSRI)^35^	✓	✓	✓	✓
Childhood Trauma Questionnaire (CTQ)^36^	✓	✓	✓	✓
Illness Perception Questionnaire-Revised^37^	✓	✓	✓	✓
